#### Fecal microbiota transplantation.

Oral gavage with fecal material from patients with AN or HCs (in the AN-FMT and HC-FMT groups, respectively), or with PBS containing 10% glycerol (in the Sham group), will be performed a total of seven times during the initial mouse experiment (Fig 3B). The processed anaerobic fecal samples from WP1 (see section “Fecal samples”) will be thawed at approximately 37°C and thoroughly mixed. Thawed samples will be used for oral gavage within 2 hours, using a 24G ball-tip steel gavage needle. Each oral gavage administration will consist of 100 µL, an appropriate volume for mice weighing 10 g or more.

#### Assessing anxiety- and compulsive-like behaviors in mice.

In mice, anxiety- and compulsive-like (i.e., repetitive) behaviors can be assessed using several well-established behavioral tests, including the OF, EPM, and MB tests [66] (**Fig 6**). The EPM consists of a plus-shaped apparatus elevated above ground, with two open arms and two closed arms. The EPM is a well-established behavioral test that assesses anxiety-like behavior based on the natural conflict in rodents between the drive to explore and the aversion to bright, open, and elevated environments. The open arms, combined with the elevated platform, create a mildly aversive environment that enables assessment of this exploration-avoidance conflict. More time spent in the open arms is interpreted as reduced anxiety-like behavior, whereas preference for the closed arms indicates higher anxiety levels. The OF consists of a square box with four walls and assesses anxiety-like behavior and locomotor activity, based on the assumption that anxiety suppresses an animal’s drive to explore novel environments, while reduced anxiety promotes exploration. One commonly observed behavior in the OF test is thigmotaxis, meaning the tendency to remain close to the walls and corners of the arena while avoiding the exposed center. Mice that exhibit higher locomotor activity, increased rearing, and reduced thigmotaxis are generally interpreted as less anxious and more explorative. The MB test is conducted in a standard bedding-filled cage, where a set number of glass marbles are evenly spaced on the surface of the bedding. The MB test primarily assesses compulsive-like, repetitive behavior in rodents, and to some extent, anxiety-related responses. The tendency to bury marbles is considered a form of species-typical digging behavior that may be exaggerated in the context of heightened arousal or compulsivity.

**Fig 6 pone.0342275.g006:**
[figure not shown]
Behavior tests for assessing anxiety- and compulsive-like behaviors in mice. **(A)** Elevated plus maze **(B)** Open field test **(C)** Marble burying test. Created with BioRender.com. (C) is based on template; Marble burying Behavioral test.

#### Sample size estimation: number of FMT donors and recipient mice.

The initial experiment in WP3 will have 32 mice in the AN-FMT group (eight AN donors, four mice per donor), 32 mice in the HC-FMT group (eight HC donors, four mice per donor), and at least 6 mice in the Sham group. Thus, within the AN-FMT and HC-FMT group, there will be eight 'donor groups' with four mice in each. The number of mice in the AN-FMT and HC-FMT groups was determined through power analyses based on previously published studies with similar research objectives [36,38], together with our own experience (not published), to ensure adequate statistical power.

The OF behavioral variable total distance (cm) moved was used as response variable in the power analyses and the following assumptions were made: (A.1) Mean in HC-FMT = 3510 cm (based on a pilot experiment with C57BL/6JRj mice, **S4 File**); A.2) Mean in AN-FMT = 2317 cm (66% of HC-FMT, based on Maschek et al. [38] and Hata et al. [36]); (A.3) Standard deviation within a donor group = 749 cm (our data); (A.4) Standard deviation of donor group means = 527 cm (~15%, slightly upscaled from Hata et al. [36]’s 13% for 20-min vs. 10-min tracking). Because these assumptions are based on limited data, we used them to simulate realistic datasets across varying donor numbers (4–8 donors per group) and donor group sizes (2–14 mice per donor). Here, “realistic” means maintaining the 34% lower mean in AN-FMT while introducing random variation among donor group means and individual mice. For each combination of donor numbers and group sizes, 500 datasets were simulated (R code #1 in **S4 File**), totaling 30,000 datasets (500 × 5 × 12). **Supplemental Fig 1** in S4 File shows examples of simulated datasets.

For each of the 30,000 simulated datasets, a linear mixed model was fitted with Group (AN-FMT vs. HC-FMT) as a fixed effect and donor as random effect. Simulation-based power analyses were then performed for all models (R code #2 in S4 File). The results from the power analyses are summarized in **Supplemental Fig 2** and **Supplemental Table 1** (S4 File). Since 96% of datasets with eight donors per group and four mice per donor achieved >80% power, and 100% yielded p < 0.05 for the Group effect (green in Supplemental Table 1), a sample size of 32 mice per group (eight donors × four mice) was deemed sufficient to detect significant differences in OF total distance moved. Power estimates were similar for three mice per donor (blue in Supplemental Table 1, S4 file), but insufficient for two per donor (red in Supplemental Table 1, S4 file). However, due to potential cage effects, mice from a single donor will be split across (at least) two cages, resulting in (at least) four mice per donor group.

### Hypotheses in WP3

The mouse experiments in WP3 are and will be designed to test the following hypotheses.

WP3, Hypothesis 1: Mice receiving gut microbiota from patients with AN via FMT (AN-FMT mice) will exhibit different responses compared to mice receiving gut microbiota from HC donors (HC-FMT mice). These responses (hypothesis) are expected to include but not be limited to food intake (lower in AN-FMT vs. HC-FMT mice), body weight development (less increase in AN-FMT vs. HC-FMT mice), anxiety- and compulsive-like behaviors (more in AN-FMT vs. HC-FMT mice), alterations in gene expression profiles in discrete brain regions connected to anxiety, and appetite and metabolic regulation, and gut-barrier functions (impaired in AN-FMT vs. HC-FMT mice).WP3, Hypothesis 2: AN-related phenotypes in AN-FMT mice, such as reduced appetite, impaired body weight development, elevated anxiety- and compulsive-like behavior, and disrupted gut health, can be reversed by modulating the gut microbiota through targeted prebiotic treatment.

### Ethics approval and consent to participate

This study was conducted according to the guidelines laid down in the Declaration of Helsinki, and all procedures involving human participants (in WP1), and participant-derived samples and data (in WP1–3), were approved by the Regional Committee for Medical and Health Research Ethics, South East A on June 27, 2023 (REK ID number 588768) and Norwegian Agency for Shared Services in Education and Research (SIKT ID number 386069). The NORMA study is also registered with the National Institutes of Health Clinical Trials (www.ClinicalTrials.gov; Identifier: NCT06144905, registration date: September 22, 2023). All participants, both patients with AN and HCs, provided informed online consent to participate. Unless consent is actively subtracted, all data and material collected can be used in the NORMA study, including follow- up information collected from the National health registries. The initial mouse experiment in WP3 will be performed with permission from the Norwegian Food Safety Authority (FOTS ID31150). Handling and care of mice will be conducted in accordance with guidelines, terms and conditions determined by the EU-commission (directive 2010/63) and the Norwegian regulation concerning the use of animals for scientific purposes. Protocol modifications involving WP1 and WP3 must be approved by REK and the Norwegian Food Safety Authority, respectively. Authorships will follow Vancouver guidelines.

### Consent for publication

All participants, both patients with AN and HCs, provided informed online consent for publication of the results.

## Discussion

By joining forces of researchers, clinical health care services, and voluntary sector, the NORMA study aims to improve our understanding of the role of the gut microbiota in patients with AN. Together, the three WPs that comprise the NORMA study—a clinical observational trial (WP1), in vitro fermentation experiments (WP2), and animal experiments (WP3)—will offer a unique, multidimensional, and transdisciplinary approach to investigate the gut microbiota and its interaction with GBA in AN. Not only will we consider factors like diet, medications, and GI complaints (WP1), but we will also, in the preclinical experiments (WP2 and WP3), explore potential underlying mechanisms and therapeutic targets, such as prebiotic treatments. The results of the NORMA study will therefore pave the way for more effective and tolerable weight restoration strategies, as a long-term goal. To our knowledge, the targeted use of prebiotics to normalize AN-related microbiota dysbiosis has not been explored previously.

While the fecal material collected in WP1 is the foundation for the preclinical experiments in WP2 and WP3, the main aim of the clinical observational trial is to explore the gut microbiota in patients with AN before, during, and after standard care treatment. We consider these investigations crucial due to the relatively few studies so far that have examined the relationship between gut microbiota and AN [19,33,48]. Importantly, many of the previous studies of gut microbiota in AN have significant limitations, including small sample sizes (9 out of 15 studies with n ≤ 25), reliance on cross-sectional designs [18,27,30,31,67,68], and the absence of control groups [34,69,70]. Furthermore, among the largest studies, which include between 55–93 patients with AN [11,18,24,26,32,69], essential factors like diet [18,24,32], antibiotic use [24], and other variables that significantly influence the gut microbiota composition are often inadequately addressed, as highlighted in two recent systematic reviews [19,33]. The use of different methodologies and the absence of a standardized definition of ‘gut microbiota dysbiosis’ further complicate interpretations [33] and make it difficult to identify therapeutic targets to develop microbiota manipulative treatments.

Due to the limitations of the previous studies on gut microbiota in patients with AN, there is a clear need for larger-scale, longitudinal studies. While existing research suggests that microbial mechanisms may play a role in the etiology of AN [18,26], more evidence is needed to determine whether gut microbiota dysbiosis is a consequence of the disorder, a contributing factor to its onset, or involved in its maintenance. The NORMA study will address these gaps by combining a well-powered clinical observational trial accompanied by animal and in vitro experiments, integrating detailed dietary and medical data, and standardized and validated methodologies. This approach allows for a more accurate assessment of microbiota changes over time but also provides insights into the underlying mechanisms. The remainder of the discussion outlines the core strengths of the NORMA study, as well as key methodological aspects to consider in relation to the current research protocol.

In addition to being one of the largest longitudinal studies of gut microbiota in AN—including patients from six hospitals across Norway— the NORMA clinical trial benefits from several major methodological strength: firstly, the high adherence of all patients—primarily inpatients—to specialized treatment programs for EDs throughout the research period. This adherence results in a consistent treatment framework, including structured routines, and dietary interventions across the patient cohort. Although minor differences in therapeutic approaches and nutritional treatment will exist across hospitals, the overall consistency will reduce the risk of confounding factors. This uniformity represents a significant methodological advantage compared to studies primarily involving outpatient populations, where treatment heterogeneity is typically greater.

Furthermore, the data collection in WP1 is conducted at three time points, allowing us to distinguish between the acute effects of re-nutrition after 6 weeks and the more long-term effects after 12 weeks of treatment. Some studies describe a ‘microbiota shift’ during treatment [25,26,32], but more insight is needed to pinpoint when this shift occurs, as only one of the five longitudinal studies in the field includes more than two time points for data collection [26]. It should also be noted that the NORMA study has received approval to track patients for up to ten years after enrollment. This includes permission to collect additional data from medical registries and hospital readmissions, providing a valuable opportunity for long-term analysis. This will provide the opportunity to further explore whether the gut microbiota could serve as a prognostic marker for readmission, recovery, and other AN-relevant outcomes, as proposed by Andreani et al. [26].

The NORMA clinical trial also stands out from previous studies by thoroughly assessing antibiotic use in childhood and prior to treatment, and by carefully defining exclusion criteria for antibiotic use (i.e., treatment with oral antibiotics in the past two months). While some studies set this exclusion period at four weeks or less [25,26,30], or not specify previous use of antibiotics [24,31], the NORMA study has opted for a longer timeframe of two months to further reduce the possibility that antibiotics influence the results.

Additionally, the inclusion of a control group at baseline is crucial due to the lack of a ‘gold standard’ for healthy gut microbiota and inconsistent definitions of dysbiosis [33]. This baseline comparison helps identify problematic aspects of AN gut microbiota. Since the core gut microbiota in healthy individuals is relatively stable over time [71], HCs are sampled at one time-point only. HCs will mainly be recruited from healthcare workers and students in south-eastern Norway. As most healthcare workers and students have moved from other regions, this will ensure a broad geographic diversity and minimizing potential regional bias in gut microbiota composition.

Finally, a key strength of the NORMA clinical observational trial is the comprehensive and detailed dietary registration, which is often lacking in previous studies. This omission in the literature is paradoxical, given how central diet is in modulation of the gut microbiota [20,72] and the fact that changes in eating behaviors and diet, are key characteristics of AN [22]. By carefully documenting dietary intake, the NORMA study may determine the extent to which dietary factors explain the dysbiosis observed in AN. The combination of using an open and detailed dietary assessment method and conducting dietary interviews performed by trained personnel or dietitians ensures the quality and reliability of dietary data. Furthermore, the study includes systematic mapping of medication use, allowing for assessment of potential associations between medication and microbiota dysbiosis, an area that, to our knowledge, has not yet been thoroughly explored in this population [19].

While the NORMA observational clinical trial will address many of the shortcomings of previous studies, some important limitations and methodological considerations must be addressed. Firstly, the study duration is limited to 12 weeks of standard care treatment which may restrict conclusions about long-term outcomes and the extent to which underweight is an explanatory factor of microbiota dysbiosis. Secondly, while the majority of the included patients will be inpatients, the patient population will also include some individuals receiving sequential treatments. However, while this approach may lead to less control over the treatment framework, it could also result in greater variability and enhance the generalizability of the findings to a broader range of patients with AN. Thirdly, a clear scope restriction is that the NORMA study focuses exclusively on females with severe AN. This decision is based on the higher prevalence of AN among females, who are disproportionately affected by its most severe forms. Additionally, including only severely ill patients allows for the advantage of studying participants in the controlled environment of specialized treatment wards, ensuring standardized care and minimizing external variables. However, this focus may reduce the generalizability of the findings to males, individuals with other EDs, and patients with less severe forms of AN, as the study population may not fully represent the broader AN patient group.

To uphold ethical research standards, the NORMA study employs in vitro experiments and in vivo ‘humanized’ mouse models in place of direct dietary interventions in patients with AN. This approach minimizes patient burden by avoiding disruptions to standard clinical treatment and reducing stress and anxiety. Furthermore, it allows for the investigation of microbiota interactions in a controlled environment, circumventing the ethical complexities associated with experimental dietary manipulation in this vulnerable population The in vitro experiments using human fecal microbiota allow for the identification of potential therapeutic targets and prebiotic treatments that can be used to manipulate the microbiota community. The prebiotic galactoglucomannan, chosen for this study, efficiently boosts the growth of butyrate-producing bacteria like *Roseburia intestinalis* and *Faecalibacterium prausnitzii*, which may be considered key targets for microbiota improvements [52] and is an important first step in exploring whether microbiota from AN would benefit from such exposure.

However, the clinical relevance of the in vitro experiments will be limited by several factors. Notably, cultivating gut microbes in bioreactors also presents challenges in replicating key physiological conditions, such as dynamic flow, microbial turnover, and spatial gradients in oxygen and pH. A particular concern is the potential loss of strict anaerobic bacteria and rare taxa, as culture-based methods can fail to preserve the full microbial diversity found in the original sample. To mitigate this, the NORMA study will adapt a rigorous protocol for sample collection and biobank preparation. Fecal samples from WP1 will be maintained under anaerobe conditions from the moment of collection until they are transferred into the anaerobe chamber for use in WP2 and WP3. Nevertheless, the culture-media employed may still induce ‘artificial’ shifts in the microbial community composition, favoring the growth of certain microbial taxa over others. Fast-growing species are likely to be overrepresented, although this remains to be systematically evaluated.

Additionally, the artificial and simplified nutrient input in the in vitro systems can only mimic aspects of local microbial metabolism and lack the complexity of the in vivo GI environment. Particularly, the in vitro system will not account for metabolic and immunological interaction with the host, such as via the GBA. The NORMA animal experiments will thus ensure that causalities are tested in a more relevant biological context which will be more representative of a human response. Still, although animal experiments and set ups for exploring behavior have been rigorously tested and utilized in numerous studies, a direct transfer to humans must be interpreted with caution. Both OF and EPM behavior tests have revealed strengths and limitations in assessing anxiety like behaviors, especially in the context of testing drugs aimed at reducing anxiety [73], which we have considered carefully in the current experimental design. Including the MB test as a measure of compulsive-like repetitive behaviors must also be considered with caution. However, employing a battery of mouse behavioral tests with complementary qualities will most likely generate a better overall picture and sensitivity for assessing potential behavioral differences imposed by microbiota differences between patients with AN and HCs.

Taken together, while the applicability of these preclinical models to humans remains uncertain, they serve as an important first step in identifying promising prebiotic supplements. If positive effects of prebiotic candidates are observed on the cultivated microbiota, future clinical trials may further explore these prebiotics in patients with AN through carefully designed supplement-based or dietary interventions.

In summary, investigating the relationship between gut microbiota, core symptoms, and dietary factors in AN is crucial, as identifying microbial patterns and their response to treatment could make gut microbiota modulation a valuable component of AN management. The NORMA study will be among the largest investigations into gut microbiota changes in response to AN treatment and uniquely integrates clinical and preclinical research to explore the role of gut microbiota in AN. By expanding knowledge in this field, there is potential to pave the way for innovative treatments, such as prebiotics and tailored nutritional guidelines, that could be seamlessly integrated into clinical practice. By addressing key factors like diet and use of medication, the study aims to generate essential insights that could lead to more effective treatments and improved patient outcomes.

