The human microbiota refers to the vast collection of microorganisms that colonize the human body, whose genomes encode more than three million genes that play a significant role in both physical and mental health [20]. The majority of these microbes reside in the GI tract and include bacteria, viruses, fungi, and other microbes [20]. Although the gut microbiota has a heritable component and is affected by age, its composition is mainly influenced by environmental factors, with diet being the most potent modulator [20,21]. Patients with AN often display abnormal dietary patterns, including low energy intake, limited food variety, and fat avoidance [22,23], and patients undergo substantial nutritional changes during treatment. Indeed, substantial evidence reveals that the gut microbiota in individuals with AN is different from healthy controls (HCs), affecting both microbial composition and function [18,24–27]. These differences are often referred to as gut microbiota dysbiosis or imbalance [2,19].

The gut microbiota in individuals with AN has been found to differ from that of HCs in several ways. Multiple studies have reported reduced bacterial richness and evenness in AN, referred to as alpha diversity [19,27–29], with one study showing correlation between reduced bacterial richness and depression as well as core ED psychopathology [28]. However, other studies have found no significant differences in diversity indices between AN and HCs [24–26,30], and findings related to beta diversity are similarly inconclusive [19]. Thus, while there is broad evidence of and compositional alterations (i.e., gut microbiota dysbiosis) in patients with AN compared to HCs [18,24–27], Scala et al. [19] highlight the lack of consensus concerning diversity and psychopathological symptoms in AN.

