## Methods

### The NORMA study

The NORMA study consists of WP1; a clinical observational trial (**Fig 1**), WP2; in vitro experiments (**Fig 2**), and WP3; animal experiments (**Fig 3**). An overview of all WPs is presented in **Fig 4**. The NORMA study is led by the Norwegian University of Life Sciences (NMBU) and conducted in collaboration with seven specialized inpatient EDs treatment units across six hospitals in Norway, located in Oslo, Bergen, Vikersund, Levanger, Bodø, and Gjøvik. Additional collaborators are The University of Oslo, Karolinska Institute and the Norwegian user organizations for eating disorders ROS and SPISFO, which has been involved in the planning of the study. WP1 includes a cross-sectional design that will investigate the microbial composition of the gut in patients with AN in comparison with HCs, and a clinical observational trial that will investigate how the composition is affected by standard care treatment in AN longitudinally (one group time-series design). We will then apply preclinical models in WP2 (in vitro fermentation experiments) and WP3 (animal experiments) based on fecal material from WP1. The first results are expected to be generated during second quarter of 2026.

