The recruitment of 90 HCs will be conducted in two phases. An initial group of HCs will be recruited primarily via a post published on the Oslo University Hospital intranet, supplemented by strategically placed posters at key locations within the hospital. Additionally, colleagues and friends may be recruited through other social networks. The second half of the HC participants will be recruited through Ås municipality and via the intranet at NMBU. The inclusion criteria concerning age will be adapted in the second phase of recruitment to ensure a more comparable age between the HC groups and patients with AN. Potential HCs will be contacted by the study researchers by email or phone and will be screened according to the inclusion and exclusion criteria. If eligible, they will sign a digital informed consent and receive all necessary information for further participation in the study.

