#### Fasting blood samples.

For the patients with AN, overnight fasting blood samples will be taken at their respective hospitals, and when possible, concurrently with regular blood samples as part of normal treatment procedures. In total, six blood samples will be collected at each time point (TP1–3): three serum tubes (5.0 mL with gel), two Ethylene Diamine Tetracetic Acid (EDTA) tubes (one 4.0 mL without gel and one 5.0 mL with gel), and one 4.0 mL heparin-coated vacuum tube. All the tubes will be inverted 4–5 times immediately after blood collection, stored at room temperature (19–25°C) for minimum 30 minutes (for clotting) and maximum 60 minutes, and centrifuged (15–20 minutes, 1100–1500 × g, 19–25°C) at the local hospital laboratories, except for the lithium heparin tube, which will be placed on ice immediately after sampling. The resulting supernatant from one of the serum samples will be aliquoted into five cryotubes at each hospital’s laboratory (i.e., five serum aliquots for each timepoint) and stored at −80°C, or for a maximum of 3 months at −20°C, before transportation to NMBU on dry ice. At NMBU, the serum aliquots will then be stored at −80°C for biobanking until further analysis. The remaining five blood samples will be analyzed at the local laboratories.

For the HCs, overnight fasting blood samples will be taken at the Regional Department of Eating Disorders at Oslo University Hospital by nurses or students who have completed an approved course in blood sampling. The HCs will collect the same blood sample types as the patients with AN, except no heparin tube, and follow the same procedures as described for the patients including aliquoting serum samples for biobanking at NMBU until further analysis. The remaining blood samples will be analyzed at the Department of Medical Biochemistry at Oslo University Hospital.

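### Region is partly confounded with AN status in the baseline AN-HC comparison, and the Discussion's assurance that regional bias is minimised is unsupported

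*Protocol article*

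**What the plan says.** **Controls.** The Discussion states that "HCs will mainly be recruited from healthcare workers and students in south-eastern Norway". Under Study participants, phase one is described as "An initial group of HCs will be recruited primarily via a post published on the Oslo University Hospital intranet", with posters in the same hospital, and "colleagues and friends may be recruited through other social networks". For phase two, "The second half of the HC participants will be recruited through Ås municipality and via the intranet at NMBU". Under Fasting blood samples, "For the HCs, overnight fasting blood samples will be taken at the Regional Department of Eating Disorders at Oslo University Hospital". The only stated step to bring controls closer to patients is on age, in phase two.

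**Patients.** The NORMA study section lists seven units in six hospitals, "located in Oslo, Bergen, Vikersund, Levanger, Bodø, and Gjøvik".

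**The assurance.** The Discussion, setting out the strengths of the control group, says: "As most healthcare workers and students have moved from other regions, this will ensure a broad geographic diversity and minimizing potential regional bias in gut". The limitations that follow do not mention where controls come from.

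**What shapes the microbiota.** The Background grants a heritable component and an effect of age, but says that "its composition is mainly influenced by environmental factors, with diet being the most potent modulator".

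**Where the comparison is used.** The AN-HC difference in composition is the first primary outcome (Outcomes). Hypothesis 2 defines normalisation as movement towards the HC profile.

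**The concern.** The protocol recognises regional bias as a threat and treats it as dealt with by an argument that does not deal with it. Two separate things are needed for the argument to work: that most controls did move from elsewhere, and that having moved makes them comparable with patients from other regions. The first is asserted without data and is not a recruitment rule. The second does not follow. Controls who moved to the Oslo area now share its surroundings, and comparability concerns where the patients live as well as where the controls grew up.

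The HC group is the study's only reference for a normal microbiota. If composition differs by region, part of the baseline AN-HC difference could be regional. A lasting offset would also leave patients from other regions some distance from the HC profile at 6 and 12 weeks, which could be read as incomplete normalisation.

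**Working it through.** **1. Side by side.** The named HC channels (Oslo University Hospital, Ås municipality, NMBU) and the single blood-sampling site are in or near Oslo. Patient units are two in Oslo and one each in Vikersund, Gjøvik, Bergen, Levanger and Bodø. Counting Oslo, Vikersund and Gjøvik as south-eastern (an assumption), 4 of 7 units overlap with the HC region and 3 of 7 do not.

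**2. The plan's own figure.** Sample size calculations gives 79 per group for 80% power at α = 0.05, raised for about 10% drop-out to 90. Check: 79 / (1 − 0.10) = 87.8, so 88; and 90 × 0.90 = 81, which covers 79. The 90 is consistent. The 79 comes from a Dirichlet-Multinomial web tool run largely on default settings that the article does not list, so it cannot be rebuilt and is not disputed.

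**3. Set-up for the illustration.** One continuous index with SD 1, 79 per group, all HCs in the south-east (a simplification), a share p of patients from outside it, and a regional shift δ in SD units. Neither p nor δ is in the article. Equal intake per unit gives p = 3/7 = 43%; 20% and 60% show the range. δ is taken as 0.2, 0.3 and 0.5.

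- Difference detectable with 80% power: (1.960 + 0.842) × √(2/79) = 0.446 SD.
- Bias in the AN-HC difference: p × δ.
- Standard error: √(v/79 + 1/79), with v = 1 + p(1 − p)δ².
- Chance of a significant result with no AN effect: Φ(−1.96 + bias/SE) + Φ(−1.96 − bias/SE).

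Example: p = 3/7 and δ = 0.5 give bias 0.214, v = 1.061, SE = 0.1615, bias/SE = 1.33, and a rejection rate of 26.4%.

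| Patients from outside | δ = 0.2 | δ = 0.3 | δ = 0.5 |
|---|---|---|---|
| 20% | 5.7% | 6.6% | 9.5% |
| 43% | 8.4% | 12.7% | 26.4% |
| 60% | 11.7% | 20.3% | 45.9% |

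At p = 43% the bias is 0.09 to 0.21 SD, or 19% to 48% of the detectable 0.446 SD.

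**4. How strong is the confounding?** With equal groups, a share q = p/2 of all participants lies outside the south-east. The correlation of region with AN status is (p/4) / (0.5 × √(q(1 − q))), which is 0.33, 0.52 and 0.65 at p = 20%, 43% and 60%. The variance inflation factors, 1/(1 − r²), are 1.13, 1.38 and 1.75. The confounding is partial, and an additive region term can be estimated.

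**5. Cost of restricting to south-eastern patients.** There are n = 79(1 − p) patients against 79 HCs, SE = √(1/79 + 1/n), and power at 0.446 SD is Φ(0.446/SE − 1.96).

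| Patients from outside | Patients kept | Power | Detectable difference |
|---|---|---|---|
| 20% | 63 | 75% | 0.473 SD |
| 43% | 45 | 67% | 0.523 SD |
| 60% | 32 | 56% | 0.590 SD |

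**The case against.** Several points on the other side are sound and limit the finding.

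- **Not every control is shown to live in the south-east.** A reader might infer that all do. The article says mainly, leaves the reach of social networks open, and does not state residence. A large south-eastern majority is likely, but totality is not documented.
- **The Background does not contradict the Discussion.** It is tempting to read it so. But the Background says mainly, names heritability, and never mentions residence. The Discussion calls the core microbiota of healthy people relatively stable, and the mouse section refers to an early critical period of establishment. Origin may leave a trace. What remains is a tension and an unsupported inference. The stability remark is made to justify one HC sample and does not address stability after moving.
- **Region and AN status can be separated in part.** A reader might conclude that no covariate can do so. The overlap of the Oslo, Vikersund and Gjøvik units with the HC region permits restriction or adjustment. Adjustment assumes the same regional effect in patients and controls, which few or no HCs outside the south-east can test.
- **The reach is limited.** Three of the four primary outcomes are changes within patients, where a constant regional offset cancels.
- **Diet is recorded in both groups**, so one likely route of a regional effect can be examined.
- **Unit is a rough stand-in for home.** Patients are referred to the units, and their residence is not given.
- **A region or site covariate may be in an analysis plan not shown.** Its absence from the article is not part of this point, which rests on the stated recruitment and the Discussion sentence.

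**Conclusion.** The point holds in a limited form. Controls come mainly from one region and patients from several, and the reason given for setting regional bias aside has no data behind it and would not secure comparability even if true. Region is partly confounded with AN status in the baseline AN-HC comparison and in distance-to-HC readings at 6 and 12 weeks; within-patient changes are largely unaffected.

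The size is unknown, because the article gives no unit counts and no regional effect. Under the assumptions in the working, the false-positive rate runs from 5.7% (20% outside, 0.2 SD) to 45.9% (60% outside, 0.5 SD). The upper end needs both a large share and a large shift. These figures illustrate sensitivity for a single index; they do not show that the AN-HC result will be wrong. This is an overstated claim with an inexpensive remedy, and it does not invalidate the design.

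**What to change.** 1. In the Discussion, withdraw the sentence that regional bias is minimised, or support it with data on controls' current residence and region of origin. List control geography among the limitations.
2. Add a sensitivity analysis of the baseline AN-HC comparison that is restricted to patients from the south-eastern units (or by home residence, if the background questionnaire captures it), adjusted for region, or both. Do the same for distance to HCs at 6 and 12 weeks. State the assumption of a common regional effect where adjustment is used.
3. Report it beside the full comparison and read it on direction and size of the estimates. It should not decide whether a difference may be called AN-related: with power of roughly 56% to 75%, real differences would often miss significance in the subset.
4. Report the number of patients per unit, so that readers can judge the overlap.

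The cost is some rewording and a secondary analysis on data already being collected. No new sampling is needed, and the full comparison keeps its precision. The downside is the wider interval in the restricted analysis, by an amount that depends on the patient mix per unit.
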